## 4 Sample size

### 4.1 Stage 1

In the Stage 1 preliminary study of the feasibility and safety of the implementation package, 4 health facilities will enrol 800 patients (~500 in Indonesia and ~300 in Papua New Guinea). Assuming 764 of these patients will have a G6PD activity >70% and be eligible for PQ7, and that the proportion of patients receiving short-course primaquine who have to stop therapy within 7 days is 5%, this sample size will produce a 95% confidence interval for the true proportion needing to stop treatment of +/- 1.55%.

### 4.2 Stage 2

**NOTE:** *Given slower than expected recruitment in Stage 1, the predicted patient recruitment in Stage 2 was revised down on 5 August 2024 to 70% of eligible patients (n=11,410) across Indonesia and Papua New Guinea. Additionally, an error was detected in the original power calculation for detection of a reduction in incidence of vivax malaria. In protocol vs 5.0, the total number of patients with vivax malaria recruited into the study was erroneously predicted to be 16,300 over 18 months (the initial timeframe for the study) when in reality this was the number of patients predicted over 12 months. This resulted in an underestimate of the monthly case incidence at each clinic and thus an underestimate of the power available for detection of an incidence reduction.*

*The revised and corrected power and precision calculations are provided below with the original erroneous calculations retained for reference. Power calculations for detection of an individual-level reduction in risk of vivax malaria recurrence are also provided.*

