### **S2.PE1 Proportion of patients with *P. vivax* malaria who correctly receive all components of revised case management**

Assuming 70% of patients enrolled into Stage 2 receive all components of the implementation package correctly, the revised Stage 2 sample size of **11,410** patients will give a 95% confidence interval for the true proportion of +/- 0.84%.

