### **S2.SE9 Safety and protocol adherence outcomes**

Assuming 1% of patients have a treatment-limiting haemolytic event, the revised Stage 2 sample size of **11,410** patients will give a 95% confidence interval for the true proportion of +/- 0.18%.

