facilities, a mean of 77 patients with vivax malaria are anticipated each month, 60% ( $n=46.3$ ) of which are predicted to be relapses and are therefore preventable. Assuming that the implementation package in Stage 2 will reduce relapses by 30%, the monthly incidence of *P. vivax* malaria is expected to fall by 13.8 (17.9%) to 63.2 cases per month. The PNG arm of the study would retain 80% power to detect a 42% overall reduction in incidence following implementation of the interventions. Furthermore assuming 70% of patients receive all components of the implementation package correctly, this sample size will give a 95% confidence interval for the true proportion of  $\pm 1.21\%$ . If 1% of patients are predicted to have a treatment-limiting haemolytic event, this sample size will be powered to determine the true proportion within  $\pm 0.26\%$ .

Results of the power calculations for the effectiveness endpoints provided above have been confirmed using numerical simulations. A total of 1000 simulated datasets from 10 health facilities, with 18 months of observations and 91 infections per month (in the pre-intervention phase) were generated. Between health-facility variation in the outcome was based on an intra-cluster correlation coefficient of 0.1, and within health-facility variation was assumed to have a standard deviation of the mean variation in monthly numbers of vivax malaria of 15 episodes per month.

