### 5.2. Stage 2 – Large-scale implementation and feasibility study

The primary analysis objective for Stage 2 is to estimate the proportion of patients with *P. vivax* malaria who correctly receive all components of revised case management (including G6PD testing, correct treatment with primaquine according to revised case management and G6PD activity, patient education, supervision of the first dose and community review at day 3), as stated in section 2.2.2. The secondary analysis objectives for Stage 2 include estimating the proportion of patients with secondary safety, tolerability and clinical review endpoints. The effectiveness and safety of implementing revised case management for patients with *P. vivax* malaria will also be estimated using an interrupted time series design for the incidence of symptomatic *P. vivax* malaria episodes, survival analysis of the cumulative risk of representation with *P. vivax* malaria and before versus

after analyses of the prevalence of asexual *P. vivax* parasitaemia and severe anaemia in patients presenting to health facilities with fever.

All of the above estimates will be presented with 95% confidence intervals.

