### 9.2. Stage 2 – Large-scale implementation and feasibility study

For Stage 2, the proportion of eligible patients receiving all elements of the implementation package correctly, and other related outcomes, will be presented for all patients, as well as stratified by study country and health facility. Corresponding 95% confidence intervals of these outcomes will be calculated assuming a binomial distribution.

The change in the incidence of symptomatic *P. vivax* malaria episodes (S2.SE15 - effectiveness endpoint) between the pre-Implementation Stage and post-implementation stage (Stage 2) will be shown graphically using an interrupted time series graph. Following the recommendations of Turner et al. (2020) the following components will be displayed: the health facility site-level (aggregated) data points versus time point of measurement (e.g. monthly for primary outcome) as a scatter plot; the interruption time will be displayed with a vertical dashed line; and the pre-interruption and post-

interruption trend lines; and the counterfactual trend line (an example is given in Appendix 3, Figure 2).

The estimate of the effect of the implementation package will be determined by fitting a segmented regression model to the monthly health facility level data (Bernal J.L. et al. 2017). For the segmented regression model, we will estimate the impact of the revised case management as:

- a) a level change comparing six months post-implementation to pre-implementation stage (Figure 2).
- b) the difference in trends before and after introduction of the implementation package (i.e. slope change comparing post-implementation to pre-implementation stage) (Bernal J.L. et al. 2017) (Figure 2).

A binary indicator variable will take the value of 1 for all time points following the start of the stage 2 implementation package within each health facility site, and a value of 0 for all other timepoints. Health facilities also participating in stage 1 will have this data excluded from analysis as seen in Appendix 4: Figure 1. A sensitivity analysis will be performed where the binary indicator variable takes the value of 1 for all timepoints following the start of implementation, including both stage 1 and 2.

See Appendix 4: Figure 1 for the data to be included in the pre- and post-implementation periods for S2.SE15.

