### Clustering

The relevant hierarchy of observations is that observations over time are clustered within health-facility. This clustering will be explored in analyses of the effectiveness outcomes using either random effects or robust standard errors for clustering by health facility.

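### Pooled and country-level confidence intervals for the Stage 2 primary endpoint ignore clustering by facility, and are too narrow by a factor that depends on an ICC the SAP does not give

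*SAP*

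**What the plan says.** Section 9.2 reports the proportion of eligible patients who receive the whole package correctly, and related outcomes, for all patients and then by country and by facility. On uncertainty it says: "Corresponding 95% confidence intervals of these outcomes will be calculated assuming a binomial distribution". Section 5.2 adds: "All of the above estimates will be presented with 95% confidence intervals".

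Section 4.2.1 gives the expected precision. For S2.PE1 it starts from "Assuming 70% of patients enrolled into Stage 2 receive all components of the implementation package correctly" and concludes that 11,410 "patients will give a 95% confidence interval for the true proportion of +/- 0.84" per cent. Under the S2.SE9 heading it takes a 1% treatment-limiting haemolytic event and concludes that the same number of "patients will give a 95% confidence interval for the true proportion of +/- 0.18" per cent.

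The SAP does recognise that observations are clustered within facilities, but its provision is limited: "This clustering will be explored in analyses of the effectiveness outcomes", by random effects or robust standard errors. Section 9.2 applies this to the incidence endpoint S2.SE15 (random intercept) and the recurrence endpoint S2.SE17 (shared frailty). Nothing extends it to S2.PE1, the other feasibility proportions or the safety proportions S2.SE9 to S2.SE13.

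**The concern.** S2.PE1 combines G6PD testing, correct prescribing, patient education, a supervised first dose and community review on day 3. In Stage 2, routine facility staff and community health workers deliver these. How well a site runs is therefore an obvious source of variation, and two patients at one site are likely to be more alike than two patients at different sites.

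The sites are few and unequal. In Table 1 the expected maximum recruitment runs from 391 to 4,690 per clinic, and the four Timika clinics hold (3,173 + 1,164 + 4,937 + 3,681) / 17,160 = 75.5% of the episodes.

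Section 2.1 says the study is to inform national policy and practice, and section 3.1 foresees wider roll-out if the changes prove feasible. For that purpose, an interval of less than one percentage point either side would claim a certainty about package delivery that ten facilities may not be able to give.

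**Working it through.** **Inputs from the SAP.** n = 11,410 (4.2); p = 0.70 and p = 0.01 (4.2.1); ten facilities with the Table 1 recruitment figures; 95% confidence, z = 1.96.

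**Assumption.** The SAP gives no ICC for these endpoints. A range of 0.001 to 0.1 is used.

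**Step 1. Reproduce the stated figures** with 1.96 × √(p(1 − p)/n):
- S2.PE1: 1.96 × √(0.70 × 0.30 / 11,410) = 0.841 points (stated 0.84).
- 1% event: 1.96 × √(0.01 × 0.99 / 11,410) = 0.183 points (stated 0.18).

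Both are plain binomial figures with no allowance for clustering.

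**Step 2. Cluster sizes.** The mean is 11,410 / 10 = 1,141. For unequal clusters the relevant size is Σm²/Σm. From Table 1 this is 47,959,080 / 16,302 = 2,942. Scaled to 11,410 patients it is 2,942 × 11,410 / 16,302 = 2,059. The scaled facility sizes run from 274 to 3,283.

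**Step 3. Design effect and half-width.** DEFF = 1 + (m − 1) × ICC, with m = 1,141 (equal clusters) or 2,059 (Table 1 sizes). The half-width is the Step 1 value × √DEFF.

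| ICC | DEFF, equal / Table 1 | S2.PE1 half-width (points), equal / Table 1 | 1% event half-width (points), equal / Table 1 |
|---|---|---|---|
| 0.001 | 2.14 / 3.06 | 1.2 / 1.5 | 0.27 / 0.32 |
| 0.005 | 6.70 / 11.3 | 2.2 / 2.8 | 0.47 / 0.61 |
| 0.01 | 12.4 / 21.6 | 3.0 / 3.9 | 0.64 / 0.85 |
| 0.05 | 58.0 / 103.9 | 6.4 / 8.6 | not meaningful as a symmetric interval |
| 0.1 | 115.0 / 206.8 | 9.0 / 12.1 | not meaningful as a symmetric interval |

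The widening factor √DEFF runs from about 1.5 (equal clusters, ICC 0.001) to about 14 (Table 1 sizes, ICC 0.1). A t quantile on 9 df in place of 1.96 adds about 15%.

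**Step 4. How much variation between sites this needs.** The between-facility SD is √(ICC × p(1 − p)). With Table 1 sizes the width doubles when DEFF = 4, so ICC = 3 / 2,058 = 0.0015. At p = 0.70 that is an SD of about 1.75 points. At ICC 0.01 the SD is √(0.01 × 0.21) = 4.6 points, and the effective sample size is 11,410 / 21.6, about 530.

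**Step 5. Coverage.** Ten facilities of the scaled Table 1 sizes were simulated from a beta-binomial model at p = 0.70 (20,000 runs). The nominal 95% exact binomial interval covered the underlying proportion 95% of the time at ICC 0, 74% at 0.001, 44% at 0.005, 33% at 0.01 and 11% at 0.1. At p = 0.01 the results were nearly the same (95%, 75%, 45%, 33% and 10%).

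**The case against.** **The ten facilities could be the target.** Section 1.2 frames the aim around ten public facilities, and section 3.1 calls the sites selected, so they are not a random sample. If inference stops at these sites, they are fixed strata and the binomial interval is not too narrow. This is the strongest defence, but sections 2.1 and 3.1 point to national policy and wider roll-out, and the SAP never limits the interval to the ten sites.

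**The SAP's own ICC does not settle the size.** A reader might infer a 14-fold error from section 4.2.2: "Between health-facility variation in the outcome was based on an intra-cluster correlation coefficient of 0.1". That simulation concerned power for the effectiveness endpoints, modelled monthly case counts, and stands under a heading marked superseded. It says nothing about a patient-level process measure and is only a reference point. Even a flat claim of several-fold is not documented.

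**Safety is weakly anchored.** A reader might infer that section 9.2 fixes binomial intervals for S2.SE9 to S2.SE13. It names no safety endpoint and no interval method for them. The binomial basis is inferred from the ±0.18% in 4.2.1 and the Stage 1 rule in 9.1. The ICC for a rare event may also be small: at p = 0.01, an ICC of 0.01 already means a between-facility SD of √(0.01 × 0.0099) = 0.995 points, about as large as the mean itself.

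**The consequences are bounded.** The point estimate does not change, single-facility intervals are unaffected by between-facility clustering, and the facility-level results will show the spread between sites. The SAP ties no test or go/no-go threshold to the S2.PE1 interval. All of this stands and lowers the severity. It does not make the pooled interval right.

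**Conclusion.** The point holds in conditional form. For inference beyond the ten sites, the pooled and country-level binomial intervals for S2.PE1 and related feasibility proportions are too narrow, and the ±0.84% in 4.2.1 shares the fault. The factor is about 1.5 to 14 over assumed ICCs of 0.001 to 0.1. Because staff at each site deliver the components, a small spread between facilities is plausible and is enough to double the width. The actual ICC is unknown until the data are seen.

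The safety part is secondary: at ICC 0.001 the ±0.18% becomes ±0.27 to ±0.32, which is less than two-fold. The single-facility intervals can stay as they are. This should be fixed because it misstates the uncertainty of the primary endpoint, but no decision rule in the SAP turns on it.

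**What to change.** **Section 9.2.** Keep the patient-weighted pooled proportion as the estimate, and name one facility-clustered interval for the pooled and country rows. One suitable choice is a GEE with independence working correlation, bias-corrected robust variance and a t quantile on (number of facilities − 1) df: 9 pooled, 5 for Indonesia and 3 for PNG. One method should be named because the alternatives estimate different things: a random-intercept logistic model gives a facility-conditional proportion unless marginalised, and a t-interval on facility proportions gives each site equal weight. With sizes this unequal, the answers can differ. Keep binomial intervals for single-facility rows. Report the between-facility range and the estimated ICC. State which interval method applies to the Stage 2 safety proportions.

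**Section 4.2.1.** Restate ±0.84% and ±0.18% over an assumed ICC range.

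**Cost.** This is a wording change and needs no new data. The stated precision becomes less favourable, and the PNG interval, on four facilities, will be wide.

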#### *Safety*

S2.SE9 The proportion of patients eligible to receive PQ who had a serious adverse event (SAE) during treatment.

S2.SE10 The proportion of patients treated with PQ experiencing at least one AESI during treatment.

S2.SE11 The proportion of patients treated with PQ with an AESI related to haemolysis during treatment.

S2.SE12 The proportion of patients treated with PQ with a gastrointestinal AESI during treatment.

S2.SE13 The proportion of patients treated with PQ with AESI related to methaemoglobinaemia during treatment.

S2.SE14 Prevalence of severe anaemia (haemoglobin < 7g/dl) in patients presenting with fever in the Pre-Implementation Survey versus the late Post-implementation Survey (derived from the quantitative surveys).

- Median and distribution of haemoglobin concentrations will also be presented for each survey

*Effectiveness*

- S2.SE15 The monthly incidence of confirmed symptomatic *P. vivax* malaria episodes (mono-infection or mixed) in the Pre-Implementation (12 months) versus Post-Implementation Stage 2 ((a) level change in 6 months post implementation (i.e. period between 6 and 12 months post-implementation), (b) change in trend of incidence immediately post-implementation (i.e. entire 12 month period post-implementation)).
- S2.SE16 Prevalence of *P. vivax* parasitaemia in patients presenting with fever in the Pre-Implementation Survey versus the Post-Implementation Survey during Stage 2 (derived from the quantitative surveys).
- S2.SE17 Cumulative risk of representation to the same health facility with symptomatic *P. vivax* malaria within 6 months in the Pre- and Post-Implementation Stages.
- S2.SE18 Cumulative risk of representation to the same health facility with symptomatic *P. vivax* malaria within 6 months in the Post-Implementation Stage for patients enrolled and not enrolled in SCOPE.

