## 7 Outcomes and Covariates

The primary, secondary and exploratory outcomes for Stage 1 and Stage 2 are defined in Section 2.2 (Endpoints).

Intervention and covariate variables for analyses of the impact of the implementation package on incidence of symptomatic *P. vivax* malaria (effectiveness outcome S2.SE15) will be defined as follows:

- a) **Level change** intervention effect (i.e. change in mean monthly incidence) 6 months after the start of stage 2; Figure 2, Section 9.
- b) **Slope change** intervention effect (i.e. change in the rate of change of monthly incidence) immediately after the start of stage 2; Figure 2, Section 9.

Intervention will take the value of 1 for all time points following the start of stage 2 implementation at each health facility site, and a value of 0 for all other timepoints for both the level and slope changes.

The time month covariate will be defined as the number of months after the start of stage 2 implementation (Appendix 4: Figure 1), i.e. negative values for pre-implementation and positive values for post-implementation.

Seasonality will be captured using spline terms for the Indonesian health facility sites and the PNG health facility sites.

Any unexpected stock outages or major, discrete malaria control interventions external to the SCOPE project will also be captured and reported by health facility site and calendar time month.

The key covariates that will be included in the analyses of the safety and exploratory outcomes will be the haemoglobin concentration at enrolment, the mg/kg dose of primaquine and the G6PD enzyme activity. Key covariates to be adjusted for in the analysis of patient-level effectiveness outcomes will be baseline age, weight and sex, except in the case that these variables have already been considered in a propensity score matching process.

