The model will include time (month) as a continuous variable, a binary variable for the implementation intervention (see (a) and (b) above), an interaction between elapsed time (since implementation) and the implementation, seasonal variation in malaria (captured using splines), adjusted for potential time-varying confounding variables including large scale malaria control activities outside of the SCOPE study and unexpected antimalarial stock outages, and allowing for a random effect for intercept to account for clustering by health facility site (Turner SL et al. 2021).

For the effectiveness outcome S2.SE15, monthly incidence of symptomatic *P. vivax* malaria will be calculated using clinic catchment populations provided by health facilities (or if not available, the most recent census). Incidence rate ratios (IRRs) (95% CIs) for the intervention effect will be estimated from a negative binomial regression model fitted to the monthly aggregated data.

**Figure 2.** Example impact model for the implementation package on the effectiveness outcome measure S2.SE15 (incidence of symptomatic *P. vivax* malaria infections). An impact model with an immediate change in level and slope. While immediate level change is allowed to occur in this model at the time of implementation, the estimand of interest with regards to level change will be calculated 6 months after implementation (at 12 months) relative to the implementation timepoint (at 6 months).

[figure not shown]

For comparison of outcomes S2.SE16 (the proportion of febrile patients with asexual *P. vivax* parasitaemia by microscopy) and S2.SE14 (the proportion of patients with severe anaemia (haemoglobin < 7 g/dl), determined from cross-sectional surveys in the pre- and post-implementation periods), prevalence ratios (95% CIs) for the intervention effect will be estimated from log-binomial regression models, and if there are convergence issues, Poisson regression with robust variance will be performed (Barros AJD & Hirakata VN 2003).

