| Normal                                                |                     |                               |
| Intermediate All                                      |                     |                               |
| Intermediate Females                                  |                     |                               |
| Intermediate Males                                    |                     |                               |
| Deficient                                             |                     |                               |
| Unknown                                               |                     |                               |
| Treatment                                      |                     |                               |
| PQ7                                                   |                     |                               |
| PQ14                                                  |                     |                               |
| PQ8W                                                  |                     |                               |
| None                                                  |                     |                               |
| Unknown                                               |                     |                               |

N = Total number; x (x, x) = median (lower quartile, upper quartile).

**Table 7. Estimates of the effect of the implementation package on the incidence of symptomatic *P. vivax* malaria episodes**

|                                                                     | Pre-implementation              | Post-implementation             | Post- versus pre-implementation |
|---------------------------------------------------------------------|----------------------------------------|----------------------------------------|----------------------------------------|
| Effect of intervention 6 months after date of implementation | Est of IR (lb, ub)                     | Est of IR (lb, ub)                     | Est of IRR (lb, ub)                    |
| Effect of intervention on slope after date of implementation | Est of change in IR per month (lb, ub) | Est of change in IR per month (lb, ub) | Est of slope change (lb, ub)           |

Est (lb, ub) = Estimate (lower bound of 95% CI, upper bound of 95% CI), IR – Incidence Rate, IRR – Incidence Rate Ratio

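### The S2.SE15 level change is not tied to the counterfactual at month 6; read literally, the Figure 2 caption adds six months of background trend to it

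*SAP*

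**What the plan says.** The SAP describes the S2.SE15 level change in five places.

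- **Section 2.2.2, S2.SE15:** "level change in 6 months post implementation (i.e. period between 6 and 12 months post-implementation", set against a 12-month pre-implementation period.
- **Section 7:** an "intervention effect (i.e. change in mean monthly incidence) 6 months after the start of stage 2". No comparator is named.
- **Section 9.2(a):** "a level change comparing six months post-implementation to pre-implementation stage", with a pointer to Figure 2.
- **Section 9.2, Figure 2 caption:** the model allows an immediate step, but the level-change estimand "will be calculated 6 months after implementation (at 12 months) relative to the implementation timepoint (at 6 months".
- **Appendix 3, Tables 7 and S3:** the row is labelled "Effect of intervention 6 months after date of implementation". The columns hold a pre-implementation rate, a post-implementation rate and a post-versus-pre IRR.

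Section 9.2 fixes the model: "The model will include time (month) as a continuous variable, a binary variable for the implementation intervention", an interaction with elapsed time, seasonal splines, and a negative binomial likelihood reported as IRRs. Section 7 counts months from the start of Stage 2, with negative values before it. The counterfactual appears only as something to draw: "and the counterfactual trend line (an example is given in Appendix 3, Figure 2". Nowhere does the text say that the month-6 IRR is taken against it.

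**The concern.** An interrupted time series separates an intervention effect from a trend that was already under way. It does so by comparing the fitted value after the interruption with the pre-interruption trend projected to the same month. The caption names a different reference, the implementation timepoint six months earlier. A ratio of month 6 to month 0 moves with any background trend, even when the package does nothing.

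S2.SE15 is the incidence endpoint for which Section 4.2.1 gives power. If its level effect is computed as the caption reads, a background decline is credited to the package and a background rise is charged against it. With several wordings in the plan, two analysts could also report different IRRs from the same fitted model.

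**Working it through.** **The plan's own figure.** Section 4.2.1 predicts a fall from 135.8 to 118.69 cases per clinic per month at 70% recruitment: 135.8 × 0.6 × 0.3 × 0.7 = 17.11. With an SD of the difference of 15 and 10 clinics, the paired t-test noncentrality is 17.11 / (15/√10) = 3.61 on 9 degrees of freedom. The two-sided 5% power is 89.3%, as stated, and the other five rows of Table 2 also reproduce. The predicted ratio is 118.69 / 135.8 = 0.874. This is a paired comparison of mean counts before and after, so it does not settle which contrast the segmented model should report.

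**The contrasts.** Let t be months from the start of Stage 2 and X the Stage 2 indicator, with season, offset and other covariates held fixed:

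log μ(t) = b0 + b1·t + b2·X + b3·t·X

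- Fitted, month 6: b0 + 6·b1 + b2 + 6·b3
- Counterfactual, month 6: b0 + 6·b1
- Pre-implementation line, month 0: b0
- Post-implementation line, month 0: b0 + b2

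This gives three ratios:

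1. Month 6 against the counterfactual at month 6: exp(b2 + 6·b3). There is no b1.
2. Month 6 against the pre-implementation line at month 0: exp(6·b1 + b2 + 6·b3). It equals (1) only if b1 = 0.
3. Month 6 against the post-implementation line at month 0: exp(6·b1 + 6·b3). The step is lost. It equals (1) if b1 and b2 are both zero, and otherwise only by the coincidence 6·b1 = b2.

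**Size, with assumed trends.** The SAP gives no secular trend, so the rates below are assumptions. The last column is 0.874 times the column before it.

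| Assumed trend per month | Six-month factor = ratio (2) or (3) with no effect | Ratio (2) if the true effect is 0.874 |
|---|---|---|
| −2% | 0.98^6 = 0.886 | 0.774 |
| −1% | 0.99^6 = 0.941 | 0.823 |
| 0 | 1.000 | 0.874 |
| +1% | 1.01^6 = 1.062 | 0.928 |

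At +1% per month the apparent reduction shrinks from 12.6% to 7.2%, so (12.6 − 7.2) / 12.6 = 43% of it is hidden. With no effect, a trend of 0.874² − 1 = −23.6% per year would reproduce the whole predicted reduction. If the effect were entirely an immediate step and the trend flat, ratio (3) would be 1.000 and the effect would vanish.

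**The wordings side by side.** This example assumes a trend of −10% per year, a step of 0.95 and a counterfactual IRR of 0.874 at month 6. Periods are averaged at mid-month.

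| Contrast | Effect present | No effect |
|---|---|---|
| Month 6 vs counterfactual at month 6 | 0.874 | 1.000 |
| Caption, vs pre-implementation line at month 0 | 0.829 | 0.949 |
| Caption, vs post-implementation line at month 0 | 0.873 | 0.949 |
| Section 9.2(a), read as month 6 vs pre-period mean | 0.786 | 0.900 |
| Section 2.2.2, read as mean of months 6 to 12 vs pre-period mean | 0.735 | 0.876 |

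The 0.873 in the third row is close to 0.874 only because 6·b1 = −0.053 happens to lie near b2 = ln 0.95 = −0.051. With no effect, the same contrast is off by as much as the second row.

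**The case against.** The strongest defence is that the caption belongs to an example impact model, and its two bracketed months can be read as positions on the axis. On that reading the sentence says when the level effect is evaluated (six months in, not at once) and not what it is divided by. The drawing was not available for this check and may mark the intended contrast. The rest of the plan leans the same way: the trend is modelled, the target is called an intervention effect, and the counterfactual line must be plotted.

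This is a fair reading, and it rules out saying that the analysis will certainly be biased. It does not repair the text. If the phrase is only about timing, the comparator is unstated, Section 9.2(a) and Table 7 still say post versus pre-implementation, and Section 2.2.2 still has a six-month window where the caption has a single month.

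Some stronger inferences are tempting but are not supported:

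- **That there are several fully rival definitions.** Section 7 and the Table 7 row label name no comparator and are compatible with the counterfactual contrast, and Section 9.2(a) refers to the figure. The plain clash is between Section 2.2.2 and the caption.
- **That two different seasons are necessarily compared.** Season is in the model as splines and can be held fixed. The SAP does not say whether it will be.
- **That the interrupted time series fails as a whole.** The trend is estimated and the slope change b3 is the same on every reading.
- **That the definition will be chosen after the data are seen.** The wording leaves room for this, but nothing in the SAP suggests it is intended.

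**Conclusion.** The concern holds in this form: the SAP does not fix the S2.SE15 level change as a contrast with the counterfactual, and its most explicit sentence, read literally, names one that carries 6·b1 of background trend and, on one version, drops the immediate step. On the timing-only reading the comparator is missing.

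The bias is zero if there is no background trend and the reference is the pre-implementation line. Otherwise its size depends on a trend that the SAP does not state. The illustrations of 0.941 and 0.886 under no effect rest on assumed declines of 1% and 2% per month. They are set against a predicted 0.874, which is itself a ratio of mean counts from the power calculation and not a month-6 effect.

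A reader might infer that the main Stage 2 conclusion is at risk. It is not: S2.PE1 is a proportion and is untouched, S2.SE15 is a secondary endpoint, and its slope-change part stands. What is at risk is the level-change IRR. Because the correction needs only wording, it should be made before the analysis.

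**What to change.** Define the level change once: exp(b2 + 6·b3), the fitted incidence at month 6 after the start of Stage 2 divided by the incidence projected from the pre-implementation trend at the same month. State that season, population offset and other covariates are held equal, and that the 95% CI comes from this linear combination of the fitted coefficients.

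Use the same wording in Section 2.2.2 (S2.SE15), Section 7, Section 9.2(a), the Figure 2 caption and Tables 7 and S3. In the level row of both tables, label the comparator as the counterfactual rate at month 6.

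If an average over months 6 to 12 is also wanted, give it as a separate named contrast against the counterfactual averaged over the same months. In the worked example above this would be 0.839 with the effect present and 1.000 without it.

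The cost is SAP wording only. The data, the model and the slope-change analysis stay as they are; a different linear combination of the same coefficients is reported.
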